### Randomization

The randomization will be centralized and stratified by center and parity and will be performed according to a 1:1 ratio. The randomization will be performed by nonvarying size block. A computer-generated randomization list will be carried out by a statistician before the study begins. Once a woman has been included through the filing of an electronic case report form (eCRF) directly via the internet (Clinsights software; Glassbeam, Santa Clara, CA, USA), she will retain her randomization number (if it has been assigned to her) even if she withdraws from the study or refuses randomization afterward.

Women will be randomized after episiotomy and before the beginning of the suture to receive either 75 mg of ropivacaine (Fresenius Kabi, Sèvres, France; marketing authorization number 3400957740832 [2009, RCP rev. 08/09/2016]) in a 20-ml syringe (10 ml of ropivacaine 7.5 mg/ml and 10 ml of normal saline) or 20 ml of placebo (normal saline; Fresenius Kabi, Sèvres, France; marketing authorization number 34009415 73941). The randomization list will be created by La Roche sur Yon Clinical Research Unit and transmitted to the pharmacy department of Nantes University Hospital, which will prepare the blinded products. Numbered and identically labeled boxes with the study number will be produced. Each box will contain a 20-ml vial of the study drug (ropivacaine or placebo according to the randomization number). The syringe will be prepared in a specific room outside the delivery room by a midwife or an anesthetist not directly involved in patient management. A label “ROPISIO Study” and the randomization number will be located on the syringe without any information about the product (ropivacaine or placebo) inside. Then, the syringe will be given to the clinician who will be performing the suture of the episiotomy. Thus, the clinician and the mother will be blinded.

### Study interventions

The intervention will consist of a perineal infiltration of a 20-ml blinded vial of the study drug (either 75 mg of ropivacaine or placebo, according to the randomization group) in the margins of the episiotomy. Careful aspiration before and during injection of the product should be performed to prevent intravascular injection. The entire contents of the 20-ml syringe will then be injected slowly at several points of infiltration. All planes will be infiltrated (vagina, muscle, and skin) before episiotomy repair. Infiltration will be performed by the midwife or the obstetrician who performed the episiotomy and who is experienced at performing episiotomy sutures.

Except for the content of the study drug vial, all aspects of management of the third stage of labor and early postpartum period will be identical in both study arms:
All drugs usually used in labor ward are allowed in this study, including prophylactic intravenous injection of 5 IU of oxytocin at delivery to prevent postpartum hemorrhage.Installation of a catheter for epidural anesthesia with continuous epidural infusion of sufentanil 5 μg/ml, ropivacaine 0.75%, and physiological saline serum.A protocol for administration of analgesics will be carried out at the participating centers, namely:
Level 1 analgesia is proposed to the painful patient to H2 postpartum: paracetamol 1 g.If the patient is still in pain at the end of 6 h, level 2 analgesia is proposed: paracetamol 1 g + ibuprofen 200 mg.If the patient is still in pain after 6 h, level 3 analgesia is proposed: paracetamol 1 g + ibuprofen 200 mg + tramadol 50 mg.

A meeting will be organized in each maternity unit before the beginning of the study to verify the attendants’ agreement and the understanding of the protocol and their proficiency in practicing the study procedures.

### Study assessments

A summary of the study timeline and investigations is presented in Fig. 1. Randomized women are provided with a study calendar to assist them to prospectively record data relevant to the study questionnaires. Research staff members are trained in standardized administration of all study questionnaires and data collection procedures. Midwives collecting data for the ROPISIO study during the postpartum period (H12, H24, H48, D7, M3, and M6) are blinded. Indeed, the patient medical record does not contain the result of the randomization.

### Outcome measures

#### Primary outcome measure

The primary outcome is the analgesic efficacy of ropivacaine at day 7 postpartum (midterm) measured with the NPRS, strictly superior to 3/10 on the perineal repair area. The systematic use of NPRS will allow an objective measurement of perineal pain in the postpartum period. The NPRS is a simple instrument widely used to assess pain intensity [29]. The patients should rate their pain on a defined scale ranging from 0 to 10, where 0 is no pain and 10 is the worst pain imaginable. This scale has already been used in several studies that assessed perineal pain after episiotomy [28, 30].

### Secondary outcomes

#### Short- and long-term analgesic effect

Perineal pain will be measured using the NPRS in the immediate postpartum period at H12, H24, and H48 by a midwife in the maternity ward. Perineal pain will also be measured using the NPRS at 3 months and 6 months using an online questionnaire.

#### Quality of life

The impact of perineal pain on quality of life will be assessed using the French version of the SF-36 with an online questionnaire at D7, M3, and M6 [31]. SF-36 is a validated and easy-to-administer self-report quality-of-life measure for routine monitoring and assessment-of-care outcomes in adult patients. The SF-36 consists of 36 questions related to eight areas about the last 4 weeks of the respondent’s life: physical activity, life and relationships, pain, perceived health, vitality, mental limitations, physical condition, and mental health. Internal consistency reliability was 0.83 to 0.93 for the eight scales and 0.94 and 0.89, respectively, for the physical and mental component summary measures [32]. Each scale is directly transformed into a 0–100 scale on the assumption that each question carries equal weight. A lower score is associated with greater disability [33].

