**Methods/design:**

The ROPISIO study is a two-center, randomized, double-blind, placebo-controlled trial being conducted in La Roche sur Yon and Nantes, France. It will involve 272 women with vaginal singleton delivery and mediolateral episiotomy at term (≥ 37 weeks). Perineal infiltration (ropivacaine 75 mg or placebo) will be administrated just after vaginal birth and before episiotomy repair. The primary outcome will be the analgesic efficacy at day 7 postpartum (midterm), defined by the Numeric Pain Rating Scale (NPRS) strictly superior to 3/10 on the perineal repair area. Secondary outcomes will be the analgesic efficacy (NPRS) and the impact of pain on daily behavior, on the quality of life (36-item Short Form Health Survey), on the occurrence of symptoms of postpartum depression (Edinburgh Postnatal Depression Scale), and on sexual health (Female Sexual Function Index) at 3 and 6 months (long-term) using validated online questionnaires. This study will have 90% power to show approximately 30% relative risk reduction in the incidence of perineal pain at day 7, from 70.0% to 50.0%.

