#### Sexual function

The impact of perineal pain on female sexual health will be assessed using the validated French version of the FSFI [36, 37] with an online questionnaire at D7, M3, and M6. This 19-item questionnaire is adapted for both sexually active and nonactive women and allows the assessment of different aspects of sexual function (desire, arousal, lubrication, orgasm, satisfaction, and pain) over the past 4 weeks. The total score ranges between 2 and 36; higher scores are associated with a lower degree of female sexual dysfunction (FSD). A consensus seems to be found in the literature for values less than 23 to define FSD [36, 38]. A good reliability has been described for the French version with intraclass correlation coefficients superior to 0.75 and Cronbach’s α coefficients superior to 0.8, similar to the original English version. Convergent validity was assessed as excellent (100%), and discriminant validity was satisfactory (89.5%) [36].

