### Statistical analysis

Both intention-to-treat and per-protocol analyses will be conducted, following the Consolidated Standards of Reporting Trials (CONSORT) guidelines for randomized controlled trials and will be conducted with the statistician and researchers blinded to group status. The two groups will be described for demographic characteristics and risk factors for perineal pain after episiotomy. The existence of a “ropivacaine effect” (i.e., a difference between the two groups for the primary outcome measure and the secondary outcome measures) will be analyzed. In case of missing data for the primary endpoint, two types of imputation will be realized (multiple imputation and worst case imputation): NPRS strictly superior to 3/10 on the perineal repair area. The percentage of patients with an NPRS strictly superior to 3/10 on the perineal repair area at D7 will be compared between groups (ropivacaine versus placebo) by a mixed effects logistic model in order to take into consideration parity, center, and group as fixed effects. A sensitivity analysis will be performed to consider analgesic administration at H2 and D7. The analgesic consumption will be added in a fixed effects model. A generalized linear mixed regression approach will be used for three criteria: the impact of perineal pain on sexuality (FSFI), depression (EPDS), and quality of life (SF-36) at D7, M3, and M6. This analysis allows taking into account intraindividual and interindividual variability. The group and temporal effects will thus be estimated.

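### SF-36 and FSFI recall four weeks but are scored at day 7, so 64–75% of the window precedes treatment; as written, the mixed model pools that score with months 3 and 6

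*Protocol article*

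**What the plan says.** All references are to the protocol article.

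- **Quality of life:** the instrument is the "French version of the SF-36 with an online questionnaire at D7, M3, and M6", and its questions are "related to eight areas about the last 4 weeks".
- **Sexual function:** the FSFI is also given at D7, M3 and M6, and its domains are assessed "over the past 4 weeks".
- **Aim, design, and setting:** both scales are listed as secondary outcomes at all three visits.
- **Randomization:** allocation, and therefore infiltration, comes after the episiotomy and before the suture. Birth is day 0 for treatment.
- **Data management:** D7 answers are accepted until D10.
- **Statistical analysis:** one generalized linear mixed regression covers FSFI, EPDS and SF-36 at D7, M3 and M6. On what it will deliver, the text says: "The group and temporal effects will thus be estimated".
- **Abstract, Methods/design:** the secondary outcomes are placed "at 3 and 6 months (long-term) using validated online questionnaires", with no mention of D7 for these scales.

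Nowhere does the article describe a shorter-recall version, adapted D7 wording, or separate handling of the D7 scores.

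**The concern.** A four-week questionnaire completed one week after birth asks mostly about late pregnancy. A treatment given at birth cannot have changed that period. The D7 scores on these two scales are therefore largely pre-treatment measurements labelled as outcomes.

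The analysis then carries this forward. A mixed model with only group and time terms returns one group coefficient for the three visits together. That coefficient would blend the D7 score with the M3 and M6 scores, and it would not show the between-arm difference at M3 or at M6. Long-term quality of life and sexual health are among the trial's stated aims, so for these scales the reported number would not answer the question asked.

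**Working it through.** The plan gives no figure for the share of the recall window that precedes birth, so there is none to reproduce on this point. Its sample size does reproduce. For 70% v 50%, two-sided 5%, 90% power: (1.960 × √(2 × 0.60 × 0.40) + 1.282 × √(0.70 × 0.30 + 0.50 × 0.50))² / 0.20² = (1.358 + 0.869)² / 0.04 = 124 per group. That calculation belongs to the NPRS primary outcome and says nothing about SF-36 or FSFI.

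**Step 1. Share of the window before treatment.** Inputs: recall of 4 weeks = 28 days (Quality of life; Sexual function), treatment at day 0 (Randomization), completion on day d from 7 to 10 (Data management). Pre-birth share = (28 − d)/28.

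| Day completed | Days before birth | Share |
|---|---|---|
| D7 | 21 | 75.0% |
| D8 | 20 | 71.4% |
| D9 | 19 | 67.9% |
| D10 | 18 | 64.3% |

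At M3 and M6 the share is 0%.

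**Step 2. Effect on a pooled coefficient.** Assumptions, none of them in the article: respondents weight all 28 days equally; the three visits have equal weight; the effect during the first postpartum days is δ; the effect at M3 and M6 is rδ. The D7 score then carries fδ, with f = 7/28 = 0.25 at D7 and f = 10/28 = 0.357 at D10.

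Pooled effect = (f + 2r)δ/3. Its departure from the M3 and M6 effect is (f + 2r)δ/3 − rδ = (f − r)δ/3.

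| r (true M3 and M6 effect, in δ) | Pooled, f = 0.25 | Pooled, f = 0.357 |
|---|---|---|
| 1 | 0.75 | 0.79 |
| 0.5 | 0.42 | 0.45 |
| 0.25 | 0.25 | 0.29 |
| 0 | 0.08 | 0.12 |

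With a constant effect (r = 1) the pooled value is 75% of the truth, or 79% for answers at D10. (This 75% and the 75% in step 1 are different quantities.) The pooled value understates the M3 and M6 effect when r exceeds f. It overstates that effect when r is below f: with no late effect at all, it still shows 0.08δ to 0.12δ.

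**Step 3. Precision cost of setting D7 aside.** Assume equal variances and a common between-visit correlation ρ. The variance of a mean of k visits is proportional to (1 + (k − 1)ρ)/k. The SE ratio for two visits against three is √[((1 + ρ)/2) / ((1 + 2ρ)/3)]. At ρ = 0.5 this is √(0.750/0.667) = 1.06; at ρ = 0 it is √(0.500/0.333) = 1.22. For one visit against three the ratio is √[3/(1 + 2ρ)], which is 1.22 at ρ = 0.5 and 1.73 at ρ = 0.

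**The case against.** The strongest reply concerns the model. The article is a condensed account. It names group and time effects but does not exclude a group-by-time term, and it also says in general terms that group differences on the secondary outcomes will be analysed. Interactions and visit contrasts are often left to a statistical analysis plan, which is not at hand. A reader might infer that the model cannot give an M3 or M6 effect; the text does not support that. What stands is narrower: the effects the article does name would not give it. An interaction added elsewhere would separate the visits, but it would not change what a D7 score measures.

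Three other strong readings also fail.

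- **That the group effect is necessarily pulled towards zero.** This needs a late effect that is not much smaller than the early one. A single infiltration may well have a fading effect, and step 2 shows the error can then run the other way.
- **That a definite loss of power follows.** The article gives no effect size, SD or power for SF-36 or FSFI. Its 90% power is for the primary outcome.
- **That the trial's long-term question goes unanswered.** Perineal pain on the NPRS at 3 and 6 months is a separate outcome outside this model, and midterm effects are part of the stated aim.

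The abstract is weak support for removing D7, because the body consistently lists all three visits. It is also fair that randomization balances pre-birth experience in expectation, so the recall problem dilutes the D7 comparison and adds noise but does not create a false benefit at D7.

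**Conclusion.** The recall mismatch is established from the article's own text. For answers accepted from D7 to D10, 64–75% of the SF-36 and FSFI window precedes the infiltration. That range needs only the calendar; how far it dilutes the score depends on how women weight the days they recall.

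The modelling point holds in conditional form. As written, only group and temporal effects are named, and a single group effect would include the mostly pre-treatment score without giving the M3 or M6 difference. The 75–79% retention figure is an illustration under a constant effect with equal weighting of days and visits. The direction of error under other patterns is not fixed, and no power loss can be derived.

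Only secondary outcomes are touched. The D7 NPRS primary outcome, its sample size and the long-term NPRS outcomes are unaffected. No recall period is stated for the EPDS, so the recall point does not extend to it, although the pooling point does. This should be corrected, but it does not threaten the main result.

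**What to change.** Change the analysis wording while the statistician is still blinded. Enrollment is complete, so the instruments themselves are taken as given.

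1. For FSFI, SF-36 and EPDS, add a group-by-time term and report the between-arm difference with its confidence interval at D7, M3 and M6.
2. For SF-36 and FSFI, base the efficacy conclusion on M3 and M6. Report D7 descriptively and state that most of its recall window precedes treatment.
3. EPDS may keep D7 as an efficacy time point.

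No new data are needed. The cost is that visit-specific estimates are less precise than a pooled one. Under the assumptions of step 3, the SE is 6–22% larger for the mean of M3 and M6, and 22% larger for a single visit at ρ = 0.5 (73% in the extreme case of uncorrelated visits). The D7 comparison on these two scales also ceases to be an efficacy result.

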#### Pain characteristics

The pain characteristics will be assessed using the French version of the DN4 questionnaire with an online questionnaire at D7, M3, and M6 [34]. The simplified DN4 is a self-report questionnaire that can be useful in helping to diagnose neuropathic pain and consists of four questions and ten items. If the patient’s score is greater than or equal to 4/7, the pain may be considered as neuropathic [34, 35]. A cutoff score of 4 resulted in the highest percentage of correctly identified patients (86.0%), sensitivity (82.9%), and specificity (89.9%) of this ten-item questionnaire, including both sensory descriptors and sensory examination. The interrater reliability was confirmed by κ values ranging between 0.70 and 0.96 [35].

#### Sexual function

The impact of perineal pain on female sexual health will be assessed using the validated French version of the FSFI [36, 37] with an online questionnaire at D7, M3, and M6. This 19-item questionnaire is adapted for both sexually active and nonactive women and allows the assessment of different aspects of sexual function (desire, arousal, lubrication, orgasm, satisfaction, and pain) over the past 4 weeks. The total score ranges between 2 and 36; higher scores are associated with a lower degree of female sexual dysfunction (FSD). A consensus seems to be found in the literature for values less than 23 to define FSD [36, 38]. A good reliability has been described for the French version with intraclass correlation coefficients superior to 0.75 and Cronbach’s α coefficients superior to 0.8, similar to the original English version. Convergent validity was assessed as excellent (100%), and discriminant validity was satisfactory (89.5%) [36].

#### Postpartum symptoms of depression

The impact of perineal pain on mood will be assessed using the French version of the EPDS [39, 40] with an online questionnaire at D7, M3, and M6. The EPDS is a ten-item self-report scale, and the total score ranges between 0 and 30; higher scores are associated with more symptoms. EPDS has good sensitivity and specificity for identifying probable clinical postpartum depression in community samples [41] and a good reliability for internal consistency of the global scale (Cronbach’s α, 0.76), and its short-term test-retest reliability is good (0.98) [40]. A score ≥ 12 on the EPDS was used as a measure of symptoms of maternal postpartum depression [42, 43].

### Statistical analysis

Both intention-to-treat and per-protocol analyses will be conducted, following the Consolidated Standards of Reporting Trials (CONSORT) guidelines for randomized controlled trials and will be conducted with the statistician and researchers blinded to group status. The two groups will be described for demographic characteristics and risk factors for perineal pain after episiotomy. The existence of a “ropivacaine effect” (i.e., a difference between the two groups for the primary outcome measure and the secondary outcome measures) will be analyzed. In case of missing data for the primary endpoint, two types of imputation will be realized (multiple imputation and worst case imputation): NPRS strictly superior to 3/10 on the perineal repair area. The percentage of patients with an NPRS strictly superior to 3/10 on the perineal repair area at D7 will be compared between groups (ropivacaine versus placebo) by a mixed effects logistic model in order to take into consideration parity, center, and group as fixed effects. A sensitivity analysis will be performed to consider analgesic administration at H2 and D7. The analgesic consumption will be added in a fixed effects model. A generalized linear mixed regression approach will be used for three criteria: the impact of perineal pain on sexuality (FSFI), depression (EPDS), and quality of life (SF-36) at D7, M3, and M6. This analysis allows taking into account intraindividual and interindividual variability. The group and temporal effects will thus be estimated.

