## Discussion

The ROPISIO study will assess the efficacy of ropivacaine infiltration to reduce perineal pain in the postpartum period at midterm and long term and increase in the quality of life. This analgesic management could improve the women’s quality of life in the postpartum period (earlier mobilization, better interaction with the baby, decrease in analgesics used). In the long term, we expect a decrease in dyspareunia and a better overall quality of life for the women.

Most studies on analgesic management of pregnant patients focused on pain during labor or following a cesarean section. Perineal pain in association with an episiotomy has been much less studied and is often underestimated. Ropivacaine is a promising candidate drug, inexpensive and easy to administer, and infiltration with this analgesic could be added to the routine management of all women after episiotomy worldwide. The evidence currently available is too limited to justify its widespread use for perineal pain prevention in the postpartum period. This adequately powered, multicenter, randomized, placebo-controlled trial aims to determine if the risk/benefit ratio favors the systematic use of ropivacaine after episiotomy to prevent postpartum perineal pain.

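### The sensitivity analysis adjusts the day 7 group effect for analgesic use, a post-randomisation consequence of pain, so its result cannot confirm or weaken the primary result

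*Protocol article*

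**What the plan says.** The Statistical analysis section compares the proportion with a pain score above 3 at day 7 "by a mixed effects logistic model in order to take into consideration parity, center, and group as fixed effects". It then adds: "A sensitivity analysis will be performed to consider analgesic administration at H2 and D7". The next sentence gives the method: "The analgesic consumption will be added in a fixed effects model". Coming straight after the primary model, this most naturally means the same day 7 group comparison with analgesic use as a further covariate.

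Other sections show what kind of variable this is:

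- Timing (Randomization): "Women will be randomized after episiotomy and before the beginning of the suture". Infiltration also comes before repair, so use at or after H2 is later than both.
- Trigger (Study interventions): "Level 1 analgesia is proposed to the painful patient to H2 postpartum: paracetamol 1 g". Escalation follows the same logic: "If the patient is still in pain at the end of 6 h, level 2 analgesia is proposed".
- Status (Aim, design, and setting): analgesic use, by interval from H2 to day 7 and again later, is a secondary outcome.
- Expected effect (Discussion): among the hoped-for benefits are "earlier mobilization, better interaction with the baby, decrease in analgesics used".

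The article does not treat analgesic use as a baseline variable, does not name a direct-effect estimand, and gives no method for confounding that arises after randomisation.

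**The concern.** Randomisation makes the arms comparable in everything fixed before infiltration. It does not make them comparable within levels of something that happens afterwards and depends on both treatment and pain.

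Analgesic use plays two roles here. It may lie on the path from treatment to day 7 pain, so holding it fixed removes or adds part of the effect. It is also a common consequence of treatment and of each woman's underlying pain propensity. Among women who took analgesics, those on ropivacaine would tend to be the more pain-prone if the drug works early, because they needed analgesics despite it. Use recorded at day 7 may even be a response to the pain score being analysed.

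This is the only planned sensitivity analysis that addresses analgesic use. If it agrees with the primary result it will be read as support, and if it differs, as doubt. Neither reading would be justified.

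**Working it through.** **Planning figures.** The Abstract and Sample size sections give 70% versus 50%, 90% power and two-sided 5%. With mean proportion 0.60:

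n = [1.96 × √(2 × 0.60 × 0.40) + 1.2816 × √(0.70 × 0.30 + 0.50 × 0.50)]² / 0.20² = (1.358 + 0.869)² / 0.04 ≈ 124 per arm.

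This reproduces the stated 124. The planned effect as an odds ratio (OR) is (0.50/0.50) / (0.70/0.30) = 0.43, a risk difference of −0.20. The question is what the adjusted model returns when that effect is true, and when there is none.

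**Model A** (400,000 women per scenario). T is the randomised group, U ~ N(0,1) is pain propensity, A is analgesic use and Y is a score above 3 at day 7.

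- logit P(A) = 0.4 + γT + βU
- logit P(Y) = α(T) + βU + δA, with α(T) set so that the arms have 70% and 50%, or 70% and 70%

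All values of β, γ and δ are assumptions. Parity and centre are left out. Y is then modelled on T alone and on T plus A.

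| β | γ | δ | Analgesic use, placebo / ropivacaine | Adjusted OR (true 0.43) | Adjusted risk difference (true −0.20) | Adjusted OR (true 1.0) |
|---|---|---|---|---|---|---|
| 1 | 0 | 0 | 58% / 58% | 0.41 | −0.20 | 1.01 |
| 1 | −0.5 | 0 | 58% / 48% | 0.45 | −0.18 | 1.08 |
| 1 | −1 | 0 | 58% / 38% | 0.49 | −0.17 | 1.17 |
| 1.5 | −1 | 0 | 57% / 40% | 0.50 | −0.15 | 1.25 |
| 1 | −1 | −0.5 | 58% / 38% | 0.46 | −0.19 | 1.05 |
| 1.5 | −1 | −0.5 | 57% / 40% | 0.48 | −0.17 | 1.16 |
| 0 | −1 | −0.5 | 60% / 36% | 0.38 | −0.23 | 0.87 |

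- Row 1: if treatment leaves analgesic use unchanged, the risk difference is not biased. The small shift in OR comes from the non-collapsibility of odds ratios.
- Rows 2 to 4: analgesics do nothing to day 7 pain, so direct and total effects are the same. The adjusted OR still moves, and that movement is pure bias.
- Last row: without shared pain propensity the coefficient is a direct effect, but it differs from the total effect and moves the other way.

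**Type I error** (2,000 trials of 136 per arm, no treatment effect on day 7 pain, γ = −1, δ = 0): 5.05% unadjusted; adjusted, 8.8% with β = 1 and 11.9% with β = 1.5.

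**Model B** (a differently built check). Early pain is latent propensity plus error minus a treatment shift. Analgesic use is logistic in early pain with slope 0.8 to 2.5. Day 7 pain has the same structure, less k = 0 or 0.3 if analgesics were used.

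- True OR 0.43: adjusted 0.44 to 0.51.
- Early effect only, none at day 7: adjusted 1.10 to 1.33. A rebuild with k = 0 gave 1.09 to 1.26, so the upper end is approximate.
- Type I error at 248 women, slope 1.5: 9.3% in the rebuild.
- Power at 248 women: about 0.90 unadjusted; 0.68 to 0.84 adjusted, depending on slope and k. With an early effect half the size of the day 7 effect it is 0.85 to 0.89.
- If ropivacaine raised analgesic use, a true 0.43 became 0.375.

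Across both models, a true OR of 0.43 becomes about 0.38 to 0.51, and a true 1.0 becomes about 0.87 to 1.33.

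**The case against.** **It is only a sensitivity analysis.** This stands. The primary model contains parity, centre and group, and neither the endpoint nor the sample size depends on the adjusted model. A supportive analysis also has no power target, so the loss of power matters less than the bias.

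**The shift is modest.** This stands in part. A reader might infer that the adjusted analysis would contradict a positive primary result or show harm. The figures do not support that: moving from 0.43 to 0.51 keeps the direction and most of the size. An apparent harm appears only where there is no day 7 effect at all, and even then most trials would not reject.

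**The direction is unknown.** This also stands. The Discussion hopes for less analgesic use. The Background, however, describes a three-arm trial with a saline control in which 35% of women on ropivacaine went without oral analgesics, against 53% on saline (p = 0.09 across the three arms). If use rose or did not change, the attenuation would disappear or reverse. This does not rescue the analysis, because a check whose bias has unknown sign cannot be interpreted.

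**The covariate is loosely described.** H2 and day 7 could mean two time points or an interval, and any use or an amount. An indicator at H2 alone would probably distort less than cumulative use. Every reading is still post-randomisation and linked to pain.

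**Analgesics may mask day 7 pain.** The worry is legitimate, but covariate adjustment does not answer it.

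**Conclusion.** The concern holds for the sensitivity analysis and for nothing else. By the article's own account, analgesic use follows randomisation, is prompted by pain, is an outcome and is expected to respond to treatment. The group coefficient adjusted for it is biased for the total randomised effect. It would be a valid direct effect only if no unmeasured pain propensity drove both analgesic use and day 7 pain, which is implausible when analgesics are offered because of pain. Agreement or disagreement with the primary result therefore carries no clear meaning.

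The simulated ranges (0.38 to 0.51 for a true 0.43, and 0.87 to 1.33 for a true 1.0) rest on assumed association strengths and are illustrations, not predictions. The type I error of about 9 to 12% applies where ropivacaine lowers analgesic use and pain propensity drives both variables. It would be wrong to infer that the bias always runs towards no effect, or that the trial's main conclusion is at risk.

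**What to change.** Before unblinding, remove analgesic consumption as a covariate from any model used to check the treatment effect. Rely instead on the comparison of analgesic use between arms that is already planned as a secondary outcome, and present it beside the primary result.

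If an analysis for masking of day 7 pain is wanted, make it a randomised comparison with analgesic use inside the outcome. One option is a score above 3 at day 7, or analgesics taken for perineal pain in the latest recorded interval up to day 7 (H48 to D7). Label it supplementary and define the interval and what counts as use.

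The cost is analysis wording only. The data are already planned, and sample size and conduct do not change. The composite has a real downside: it counts a dose taken days earlier the same as a high score on day 7, so its clinical meaning differs. With 70% of controls already assumed to be above the threshold, at most 30% remain to be added, so the placebo arm may approach a ceiling.
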